### 3.2. Overview of Study Participation

This randomized controlled trial will be conducted with 420 drug-involved Black women from probation, parole or designated ATI program sites located throughout communities in NYC heavily affected by HIV and STIs. Eligible women will be randomly assigned to: (1) E-WORTH consisting of an individual evidence-based Streamlined HIV Testing session followed by a 4-session group-based multimedia HIV intervention (E-WORTH) or (2) an individual Streamlined HIV Testing session alone (Streamlined HIV Testing), which will serve as the comparison condition. Both conditions will be delivered at two Fortune Society Sites (located in Harlem and in Long Island City). If participants live too far to attend sessions at these sites, Fortune staff may also deliver intervention sessions at our community research site or at a NYC DOP site approved by the appropriate DOP Assistant Commissioner. Repeated assessments will occur at baseline and 3, 6, and 12-months post intervention. For participants residing out of New York City during their follow up period, or are otherwise prevented from traveling to study sites to complete a follow up assessment, we will send a link to follow up assessments directly to the participant's e-mail on a password protected PDF document. We will conduct repeated assessments and qualitative in-depth interviews on multi-level factors that may influence the effectiveness of E-WORTH and Streamlined HIV Testing on study outcomes with Fortune providers delivering the interventions, frontline probation, parole or designated ATI program staff (e.g. probation officers), probation administrators and probation clients. Self-reported data on behavioral outcomes will be collected from participants via audio computer-assisted self-interview (ACASI). Primary outcomes will be measured via biological assay for infection by *Neisseria gonorrhea*, *trichomonas*, and *Chlamydia trachomatis*, the most common STIs found among women in NYC.

We will also conduct qualitative interviews with 20 E-WORTH participants who reported episodes of homelessness and depression when completing assessments at baseline, 3-, 6- and/or 12-month. The goal of these interviews is to better understand the relationship between

homelessness and depression among women involved in the criminal justice system who are also at risk for HIV and other STIs.

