#### 3.4. Assessments:

Participant Assessment for Aim 1: When a participant arrives for their pre-intervention assessment, they will undergo a shortened version, 5 minutes, of the screener to confirm eligibility. If a woman no longer meets eligibility criteria, she will be compensated \$10 and will no longer participate in the study. Women who meet eligibility criteria will undergo a pre-intervention assessment. This assessment will last approximately 60 minutes, consisting of demographic information, history of criminal justice involvement, drug and alcohol use and dependence, sexual and drug-related HIV behaviors, HIV treatment and care, intimate partner violence, depression and PTSD, service utilization, and social support. RAs will schedule repeated assessments with participants that will take place at baseline and at 3, 6, and 12 months post- intervention. For all assessments, participants will complete the ACASI surveys on computers with headphones at a computer work station designed for privacy so that others cannot see their responses on the computer. Participants will be given the option to complete the baseline survey at SIG's community research office at [name] or on site at Probation, parole or designated ATI program or Fortune Society sites.

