Passive recruitment will involve flyers and advertisements that may be posted or electronically delivered in locations in probation, parole or ATI program sites and community-based organizations that provide services to women on probation, parole or an ATI program.

In addition, the Project will play a video at Department of Probation, parole or ATI programs sites for the sole purposes of recruiting new participants in the study. The video will be played on DOP, parole or ATI program screens in areas in which women wait to be seen by probation, parole or an ATI program personnel.

In addition, study participants or women from probation, parole or an ATI program who screen ineligible will be asked to refer other potentially eligible women on probation, parole or an ATI program without revealing the exact eligibility criteria. Screened participants will also be asked to refer individuals to the study using a coupon referral system. We have successfully used these recruitment strategies in our past and current RCTs that we have conducted in probation.

Research staff will then ask the woman to meet in a private room to discuss screening procedures. This private room is in an area away from probation, parole or an ATI program staff and other clients. If the woman participant is not comfortable completing a face-to-face screening at the probation, parole or an ATI program office, research staff will arrange one of two alternate procedures: 1-the participant will be scheduled with a face-to-face screening interview at the Social Intervention Group research site, or 2-the participant will be instructed to call the study 1-800 number when she is in a private setting in order to be screened by phone. At the conclusion of screening, if the female on probation, parole or an ATI program meets eligibility criteria for the study and is willing to participate, a baseline assessment will be scheduled at the Probation, Parole or an ATI Program Site or the SIG Community Research Site. When a participant attends the baseline assessment, she will first be administered a brief confirmatory screener to re-establish major eligibility criteria (if the baseline occurs more than 24-hour after the initial screening). If the participant no longer meets eligibility criteria, she will be given \$10 in compensation and will no longer participate in the study.

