## 10. Privacy Protections

All face-to-face screening interviews and face-to-face in-depth interviews will take place in a private room either at the probation, parole or an ATI program site, a Fortune site or at our community research site.

All ACASI (Audio Computer-Assisted Self Interview) interviews will take place in an enclosed cubby space or kiosk with head phones so that others may not hear questions or view responses. Although some research activities may take place within a criminal justice setting, all information collected in the interview is confidential, and will not be shared with any criminal justice entity. This includes information about illegal activity, such as drug use. Probation, parole or ATI program department personnel have affirmed that they will not seek identifiable information on research participants. The only instance where research staff are required to release identifiable information is in the case of imminent harm to yourself or others, or if there is a report of child abuse or neglect. We have obtained an assurance letter from Fortune Society and Memorandum of Understandings (MOUs) from the NYC Departments of Probation, Parole and designated ATI programs providing assurance that they will not seek the data collected about subjects. The general letter of introduction will be composed for the intervention team to introduce them to the supervisors of each probation, parole or an ATI program site where recruitment is to occur, with instructions to provide a copy of the letter to all probation, parole or ATI program officers at each such site. The researchers have taken steps to assure privacy and the confidentiality of the information provided by the participants. These steps include obtaining a Certificate of Confidentiality and the assurance of Fortune Society that it will not disclose any information to others or seek access to it. Further, probation, parole or ATI program sites will not have any documents linking the participants name to any information given to the researchers. In the criminal justice system, however, there are no absolute guarantees of confidentiality. If participants have signed a waiver of confidentiality or release (or sign one in the future), the holder of such a waiver or release may seek to obtain information from the researchers. The researchers will resist disclosure of such information by all lawful means.

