## 11. Potential Risks

Screening, assessments, and interventions should pose minimal risks to subjects participating in the study. Subjects may become embarrassed or uncomfortable while being asked questions and there is some risk that discussing sensitive topics will cause distress. Because subjects will take part in a group intervention, there is a risk that other group members may divulge confidential information to people outside the group. We will address this by asking everyone to respect the confidentiality of the other participants. Participants will be advised that conversations about HIV and safer sex negotiation may anger their male partners. This anger may put them at risk for emotional, physical and/or sexual abuse or abandonment of the relationship. Participants will be advised to observe any signs of such anger in their partners and to discuss them with study staff immediately.

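### Remote follow-up by e-mailed link has no stated privacy check or record of mode, although the protocol promises a private station for all assessments

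*Supplement*

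**What the plan says.** Section 3.2 opens a remote route for follow-up: "we will send a link to follow up assessments directly to the" participant's e-mail address, inside a password-protected PDF. It covers women living outside the city and those who "or are otherwise prevented from traveling to study sites to complete a follow up assessment", a category with no further limit.

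Section 3.4 describes a different setting: "For all assessments, participants will complete the ACASI surveys on computers with headphones at a computer work station designed for privacy". Section 10 repeats the promise for privacy reasons, saying that all ACASI "interviews will take place in an enclosed cubby space or kiosk with head phones so that others may not hear questions or view responses". Neither section mentions the remote route.

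Section 3.4 lists the content of the assessment, which includes "sexual and drug-related HIV behaviors, HIV treatment and care, intimate partner violence, depression and PTSD". Section 5 uses the same instrument at baseline and at 3, 6 and 12 months, and no shortened remote form is described.

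Section 11 warns that conversations about HIV and safer sex may anger male partners, and adds: "This anger may put them at risk for emotional, physical and/or sexual abuse or abandonment of the relationship".

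The Data Analyses Plan names the number of condomless acts as a primary outcome, modelled over the whole follow-up period. Section 1.2 lists drug use and partner violence as secondary outcomes. The model terms are assignment, the baseline value of the outcome and selected sociodemographic variables.

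**The concern.** Followed as written, the plan does not keep its own privacy promise for women followed remotely. They may be asked about violence by a partner, condomless sex and drug use in a room that the study knows nothing about. The protocol itself treats partner abuse as a risk in this population, so the hazard is foreseeable. It falls on each remote woman, however few there are.

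There is also a measurement issue. A woman who can be overlooked may answer differently from one in a closed booth. Remote and on-site answers enter the same models, and the plan does not say that they can be told apart.

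**Working it through.** No plan figure is at issue, so the check is a comparison of the text, followed by the algebra of the mode effect.

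**The text**

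1. *Setting.* Section 3.4 speaks of all assessments, and Section 10 of all ACASI interviews. Section 10 could be read as not covering a survey done elsewhere, but the wording of Section 3.4 leaves no such room. Section 3.2 allows follow-up away from any station. The three sections cannot all hold.
2. *Content.* Sections 3.4 and 5 together put the partner-violence, sexual and drug items on the remote form.
3. *Safeguard.* The only one stated for the remote route is the password on the PDF. It controls who can open the link, not who is in the room when the woman answers.
4. *Possible substitutes.* Section 8.1 has research assistants go through consent at all follow-up assessments. Section 3.8 has locator data verified at every assessment and contact made every two weeks. Section 3.3 has a checklist completed each time a woman is assessed. None of these states a privacy check. The questions about location and company in Section 3.4 concern use of the E-WORTH web program. The distress procedure in Section 11 starts from staff observing the respondent, and no remote counterpart is given.
5. *Analysis.* The Data Analyses Plan has no term for mode. Its examples of sensitivity analyses (distribution, heteroscedasticity, independence) do not include mode.

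**Effect on the between-arm comparison**

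For arm k, let s_k be the share of follow-ups done remotely and u_k the proportion by which remote answers under-report acts. Assume the same true mean for remote and on-site women within an arm. The observed rate ratio is then

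R_obs = R_true × (1 − s_1·u_1) / (1 − s_0·u_0).

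If s_1 = s_0 and u_1 = u_0, the factor is 1 and the ratio is unbiased. What remains is extra noise and blurred change from baseline. Bias needs a difference between arms in s or in u, and the documents give neither quantity.

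**How many women**

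No expected remote share is given. As an assumption only, take 5% to 20% of the 378 women in the power calculation (Section 2.3): 378 × 0.05 = 18.9 and 378 × 0.20 = 75.6, or about 19 to 76 women per visit.

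**The case against.** The strongest reply is that this is a gap in wording on a route that already has protection and staff contact. Several parts of it stand.

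- A reader might infer that a partner who shares the mailbox can read the questionnaire. The link sits inside a password-protected PDF, so he would also need the password. The documents do not say how the password is delivered. Only the risk from someone present while she answers follows directly from the text.
- A reader might take Section 7 as a general privacy rule for telephone contact, because it has a woman "instructed to call the study 1-800 number when she is in a private setting". That instruction is for women uncomfortable with screening at the supervision office. Section 3.3 allows telephone screening when no private room is available and adds no privacy condition.
- A reader might infer that Section 11 predicts abuse from the questionnaire. It concerns conversations about HIV and safer sex. It shows that the protocol recognises the hazard, not that remote follow-up has caused harm.
- Silence is not proof that mode goes unrecorded. The checklist and the policies and procedures manual (Section 12) are not shown. The fair statement is that recording of mode is not stated.
- The same remote rule applies to both arms, so a material bias in the trial's comparison cannot be claimed.

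This reply does not remove the conflict between Sections 3.2, 3.4 and 10, and it does not supply the missing check. Equal reporting across arms cannot be taken for granted either, since only E-WORTH women attend four further sessions, which discuss partner violence (Section 3.6).

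**Conclusion.** The point holds as a contradiction with a foreseeable safety consequence and a secondary measurement consequence. The plan should be changed.

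The safety part does not depend on the remote share. It rests on the content of the form, the absence of a stated check on the setting, and the protocol's own recognition of partner abuse as a risk.

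The measurement part is limited to self-reported outcomes: condomless acts, and secondary outcomes such as partner violence and drug use. A biased treatment effect is a stronger reading that the documents do not support. It needs a difference between arms in remote use or in the mode effect, and its size cannot be derived. The laboratory STI result, which drives the sample size in Section 2.3, does not depend on how the questionnaire is answered.

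**What to change.** - *Section 3.2.* Have the research assistant confirm by phone, at the follow-up consent contact already required by Section 8.1 and again when the link is opened, that the woman is in a private place and controls the mailbox. The second check matters because a call alone says nothing about a later opening. Reschedule if she cannot confirm. Provide a quick-exit and resume option.
- *Sections 3.4 and 10.* Write in the remote exception and refer to this procedure, so that the three sections agree.
- *Data collection and Data Analyses Plan.* Record mode of completion at each visit, report it by arm, and pre-specify a sensitivity analysis of the self-reported outcomes by mode, for example without remote visits. Since mode is determined after randomisation, this should remain a sensitivity analysis.

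Holding back the partner-violence section from every remote woman is not advised. Partner violence is a named secondary outcome, and the answers lost could come from the women most affected.

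The cost is protocol wording, one data field, one added analysis and a few minutes of existing staff time per remote visit. Some remote assessments will be delayed or missed. Remote follow-up and its benefit for retention are kept.

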### 3.3. Recruitment and Screening of Participants

Recruitment of participants for RCT for Aim 1: Recruitment will follow procedures that have been approved by Columbia University for recruiting participants from probation sites Projects PACT (AAAK0206), WORTH (AAAD5608) and WINGS (AAAK2851). These procedures have been refined over the course of the investigative team's multiple federally-funded studies that have successfully screened over 1000 potential participants and met target enrollment numbers of participants into HIV prevention trials. We will use various strategies for recruitment, including onsite recruitment at probation, parole or designated/selected ATI program sites, field referrals and by word-of-mouth described in detail under F Section.

Screening of participants for RCT: If a woman expresses interest in being screened for the study, the RA will describe the study and answer any questions. All potential participants will be apprised that their involvement in the study is entirely voluntary and that it doesn't fulfill any court mandate. If the woman indicates that she is willing to be screened, the RA will obtain written informed consent to be screened by reading the screening consent form to the participant and asking if she has any questions about the screening interview before obtaining her signature on the form. After obtaining informed consent, the RA will conduct a 10-15-minute screening interview to determine eligibility and willingness to participate. The screening interview will contain eligibility related items, socio-demographics, and other items that will camouflage the eligibility criteria. Interested potential participants will undergo a written informed consent and complete a 10-15-minute screening in a private room, which will consist of questions about sexual behaviors, history of drug use, and demographic information (see screening form). If a private room is not available, or if the participant wishes to be screened at a later time, the participant will be screened via phone. Once the potential participant's eligibility has been established, the RA will schedule her for an appointment to complete the baseline assessment.

The RA will ask participants who screened eligible to complete a contact information sheet that asks for their address, telephone numbers where they can be reached, and email information using a Contact information sheet. More detailed contact information (Locator Form) is obtained when participants come for the baseline assessment. In addition, participants will be asked to provide the number of children they care for directly using the Child Information Form in the event that childcare becomes a barrier to participation. Potential participants will receive a handout that introduces the study, explains compensation, and contains a contact telephone number. To ensure participants are aware of meeting times, we will send letters to remind them

of their baseline assessment, HIV testing and E-WORTH session appointment times. When potential participants are not eligible, we will send a re-screen letter after 90 days to see if they are interested in screening for the study again. At the time of the screening interview, participants will also be asked to sign a HIPAA form.

Participants will be compensated \$5 for completing the screening interview. Women who meet eligibility criteria (described below) will be asked to participate in the study, and will be told that their decision whether or not to participate in the study will not affect their status with court, NYC Departments of Probation and Parole, and designated ATI sites, or the criminal justice system. Interested participants will undergo an additional informed consent process, and will be scheduled to complete a pre-intervention (or baseline) assessment at the SIG Community Research Site. During the baseline interview, participants will be asked to provide more detailed contact information using the E-WORTH Locator Interview form. In addition, since the intervention will be delivered electronically, participants will also be asked to fill out an E-WORTH Computer Literacy Questionnaire during the baseline interview to gauge levels of computer literacy. Research Assistants will complete a study check list each time participants are assessed to ensure that all items on the check list are completed.

Recruitment of probation, parole or ATI program staff and Fortune providers for survey (Aim 4)– Prior to the beginning of the study, we will present the purpose and procedures of this study to all probation, parole or ATI program staff at the DOP study sites and to Fortune staff. After our presentation we will ask staff to participate in the survey. Staff, who are interested in participating in the study, will complete written informed consent administered by a research assistant prior to enrolling in the study. During informed consent, potential participants will be apprised that their participation in our study will not affect their position at DOP or Fortune in any way and they may withdraw from the study at any time without questions asked. For the mixed study for Aim 4, we aim to enroll 25 staff probation, parole or ATI program officers and 10 administrators (supervisory Probation, parole or ATI program Officers/Branch Chiefs/Other Managers) and the providers from Fortune Society (1 per site, n=5) delivering E-WORTH and Streamlined HIV Testing condition will be asked to complete ACASI structured survey the month prior to starting the RCT with repeated assessments every 6 months through month 45.

Recruitment of participants and probation, parole or ATI program staff for in-depth interviews (Aim 4) — From all the NYC probation, parole or ATI program sites, the Project Director will randomly select 4 women on probation, parole or ATI program who enrolled in the study (a total of 20 participants) and ask them to complete the in-depth survey. The Project Director will also randomly select 10 probation, parole or ATI program officers and 10 Probation, parole or ATI program Administrators from those who completed the ACASI structured survey and invite them to participate in an in-depth interview. In addition, the Project Director will invite all service providers from Fortune society who delivered both intervention conditions (5 service providers) to participate in an in-depth interview. The project director or an RA will contact all probation, parole or ATI program staff and study participants who have been selected to participate in the in-depth interviews by phone or mail. The project director or an RA will describe the purpose of the in-depth interview and answer any questions that randomly selected staff and study participants may have about the in-depth interviews. If staff and study participants indicate that they are willing to participate in the in-depth interview, the project director or an RA will administer informed consent.

Recruitment of participants for in-depth interviews focusing on homelessness and depression. The Project Director will identify all E-WORTH participants who reported histories of homelessness and depression when completing assessments at baseline, 3-, 6- and 12-month. Recruitment will be conducted under the direction of the Project Director by an RA and a study consultant. Interviews will be held in our offices (at the Social Intervention Group's community research site located at [name]) and is expected to last for up to 90 minutes.

